Radiological outcome will be measured by the principal investigators of the participating hospitals; data will be cross checked by the clinical investigator; dorsal and volar tilt in degrees, radial height in millimetres and ulnar variance in millimetres will be calculated directly after trauma and after 6 weeks and 6 months. Complications contain secondary displacement (radial shortening > 3 mm, dorsal tilt > 10° or intra-articular step-off > 2 mm), delayed/non-union, re-interventions, complex regional pain syndrome (CRPS), tendon injuries (ruptures and tendinitis), nerve injuries (carpal tunnel syndrome and lesions) and distal radial ulnar joint disability.

Cost-effectiveness and cost-utility of non- or minimally displaced DRFs treated by 3 weeks of cast immobilisation or 1 week of brace immobilisation will be analysed. The perspective of this study is societal, and therefore both direct and indirect costs due to the DRF will be considered. Direct costs will include treatment, follow-up visits at the outpatient clinic, additional visits to health care professionals and the treatment of complications. Non-health care related costs include expenses to travel to and from the hospital. Indirect costs are based on absenteeism of work or loss of working hours due to cast-immobilisation or pain. To estimate health care costs, the friction-cost method will be used to analyse the loss of production for an individual worker. This analysis is based on a cost-effectiveness analysis of a study on the non-operative versus the operative treatment of DRFs [27]. To analyse cost-effectiveness and cost-utility, the EuroQol 5D (EQ-5D), Productivity Cost Questionnaire (iPCQ) and the Medical Consumption questionnaires (iMCQ) will be used [28–31]. Only the applicable items are included in this study. To create baseline data, patients will be asked to complete those questionnaires at the ED at the day of trauma (*t* = 0). Patients will also be asked to complete these questionnaires at 6 weeks and 6 months.

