This study will be conducted as a single-blinded multicentre randomised clinical trial in three hospitals. In this study, 3 weeks of cast immobilisation is compared to 1 week of brace immobilisation. The inclusion procedure and the moment of randomisation are visualised in Figs. 1 and 2. Patients will be treated in a lower arm cast in a neutral position or in a prefabricated brace [32]. The follow-up after the immobilisation period will be the same for both groups and will be according to the current treatment protocol. Additional physiotherapy is advised and exercises to train wrist function will be given. The follow-up is 6 months. We used the SPIRIT checklist when writing our report [33].

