Patients can only participate if the DRF is non- or minimally displaced. They will receive written information and an informed consent form from the attending physician/the clinical investigator/research assistant. When the X-ray taken at the ED showed non- or minimal displacement, informed consent will be signed and eligible patients will be randomised (Fig. 1). An independent research assistant will perform a concealed permuted block randomisation by using a secured computer-generated randomisation schedule after stratification for gender and age. Allocation will be at random in four blocks (Table 1). In total, 1 week of brace immobilisation, if assigned to the intervention group, or 3 weeks of cast immobilisation, if assigned to the control group, will be executed. It is expected that all patients can be included within 1–1.5 year from the start of the study.

**Table 1 Tab1:** Stratification by gender and age

Patient characteristics			Randomisation
List 1	Male	< 30 y.o.a	ABAB AABB ABBA BABA BAAB
List 2	Male	> 30 y.o.a	BAAB BBAA ABAB AABB ABBA
List 3	Female	< 30 y.o.a	AABB ABBA BAAB BBAA BABA
List 4	Female	> 30 y.o.a	ABBA BABA ABAB AABB AABB

*y.o.a.* years of age, *A* 1 week of brace immobilisation, *B* 3 weeks of cast immobilisation

The inclusion and follow-up schedule are visualised in Fig. 2 and Table 2. All patients will be followed for 6 months in total. Assessments will occur at the time of admission at the ED, assessment by phone consult in 1 week after trauma (5–9-day window) in case of inclusion in the intervention group (e.g. 1 week of brace immobilisation), physical assessment in case of the control group (e.g. 3 weeks of cast immobilisation) at 1 (5–9-day window) and 3 weeks (18–24-day window). All patients will be physically assessed at 6 weeks (5–7-week window) and 6 months (5–7-month window) after the start of treatment. After removal of the brace or cast, additional physiotherapy is advised and exercises to train wrist function will be given.

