**Table 2 Tab2:**
[figure not shown]
SPIRIT figure

At each follow-up (FU) visit, the research coordinator or research assistant will ascertain patient status (i.e. secondary interventions, adverse events/complications, deaths) and will verify the information within medical records. All adverse events will be addressed to the principal investigator. The patients will be asked to indicate the actual pain level based on the VAS score, if they are currently treated by a physical therapist and if they returned to work. At 6 weeks and 6 months, the range of motion of the wrist will be measured using a goniometer.

Patients will be asked to complete questionnaires relating to disability (qDASH score and PRWE score) and medical consumption, productivity and general health to analyse cost-effectiveness (EQ-5D, iPCQ, iMCQ). Patients will be asked to complete the questionnaires at the ED as well, to generate baseline data.

Plain X-rays of the wrist will be made at the time of presentation in the hospital at the ED, after 6 weeks and 6 months. The X-ray at 6 months will be taken to determine the grade of degenerative joint changes. Time to define the presence of a delayed- or malunion will be at 6 months. Intention-to-treat principle will be maintained.

Both treatment options and used methods of treatment for this type of fracture are well known. Earlier research did not report any (serious) adverse events. All adverse events will be reported by the investigator; severe adverse events will be reported by the investigator to the sponsor of the study without undue delay after obtaining knowledge of the events. We performed an investigator-initiated risk classification: the risk of this study is expected to be negligible. Therefore, no DSMB/safety committee would be necessary. A monitoring audit will be conducted at the start of the study, after inclusion of the first 10 patients and after finishing the inclusion of patients. Also, a line listing of (serious) adverse events will be kept up and reported annually to the Amsterdam UMC Ethical Board.

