Therefore, it is important to provide level I evidence on bracing of DRFs. This study is designed as a randomised controlled trial with a non-inferiority design. Also, cost-effectiveness will be taken into account. The shorter the period of immobilisation, the earlier independency and return to work or school can be achieved, which will improve cost-effectiveness as well. Primary outcome of this study is the PRWE score after 6-month follow-up. The sample size of this study is based on the MCID of the PRWE. Functional self-reported outcome is considered as most important outcome factor. X-rays will also be analysed; however, secondary dislocation is not expected, as the non-displaced DRFs included in this study are considered to be stable. Furthermore, the correlation between radiological outcome and patient-reported outcome has been disputed in literature before. Functional outcome, especially patient-reported outcome, is the most important outcome factor. Radiological outcome does not always correlate to functional outcome, especially when aberrant outcome is subtle. But as very poor radiological outcome might influence other outcome factors, we chose to analyse this factor as well as a secondary outcome [39, 40].

This study will provide evidence on the optimal period of immobilisation in non-operatively treated displaced and reduced distal radius fractures. Both treatment options are accepted treatment protocols and both treatment options have a low risk of complications. Follow-up will be according to the current treatment protocol. This study will provide level 1 evidence on the optimal period and way of immobilisation for non- or minimally displaced distal radius fractures in adult patients.

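### EQ-5D is not collected while the two arms are treated differently (days 0-21), so a utility difference that resolves before 6 weeks adds nothing to the cost-utility result

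*Protocol article*

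**What the plan says.** Methods/design of the protocol article sets out the economic evaluation: "To analyse cost-effectiveness and cost-utility, the EuroQol 5D (EQ-5D), Productivity Cost Questionnaire (iPCQ) and the Medical Consumption questionnaires (iMCQ) will be used". Of these three, EQ-5D is the only one that yields a utility; the other two cover productivity and care use.

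The same section fixes the timing. For baseline, "patients will be asked to complete those questionnaires at the ED at the day of trauma". For follow-up, "Patients will also be asked to complete these questionnaires at 6 weeks and 6 months". The text after Table 2 (Sample and selection criteria) repeats the baseline, "Patients will be asked to complete the questionnaires at the ED as well, to generate baseline data", and adds no earlier completion.

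On treatment, Methods/design says: "In this study, 3 weeks of cast immobilisation is compared to 1 week of brace immobilisation". What comes afterwards does not differ: "The follow-up after the immobilisation period will be the same for both groups and will be according to the current treatment protocol".

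Early contacts already exist under Sample and selection criteria. The brace arm has an "assessment by phone consult in 1 week after trauma (5–9-day window) in case of inclusion in the intervention group". The cast arm is seen at 1 week and at 3 weeks (day 18 to 24). No EQ-5D is tied to any of these contacts, and no 3-week contact is stated for the brace arm.

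**The concern.** The trial expects similar function at 6 months and an earlier recovery with the brace. The Discussion puts it this way: "The shorter the period of immobilisation, the earlier independency and return to work or school can be achieved". If utility follows that pattern, the arms differ early and converge later. The utility schedule has one score at the moment of injury, before any time has been spent under the allocated treatment, and the next at about day 42, nominally 3 weeks after the cast is due off. Everything in between is filled by interpolation.

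What is at stake is the QALY part of the cost-utility result. A zero QALY difference could be reported as a finding of no quality-of-life benefit when the schedule could not have shown an early one. An analysis plan cannot repair this later, because the scores would not exist.

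**Working it through.** The article states no utility, QALY or economic sample-size figure, so there is none to reproduce. Its one design calculation (34 per arm) concerns the PRWE and does not bear on this point.

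**Inputs from the article.** EQ-5D at day 0, 6 weeks (day 42) and 6 months (about day 182). Contrast: brace against cast on days 0-7, no brace against cast on days 7-21. Visit windows: 18-24 days for the 3-week cast visit, 5-7 weeks for the 6-week visit.

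**Assumptions.** QALYs are the trapezoidal area under the utility curve. EQ-5D scores current health. The between-arm utility difference during the contrast is d = 0.05-0.20. The article gives none of these.

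**1. Weight of each planned score.**
- Day 0: 42/2 = 21 days, 21/182 = 11.5%
- 6 weeks: 42/2 + 140/2 = 91 days, 91/182 = 50%
- 6 months: 140/2 = 70 days, 70/182 = 38.5%

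Estimated QALY difference = (21 × diff at day 0 + 91 × diff at 6 weeks + 70 × diff at 6 months) / 365. If the arms are equal at these three times, this is 0 for any d in between.

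**2. True difference in that case.**

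| d | days 7-21 only: 14d/365 | days 0-21: 21d/365 | planned schedule |
|---|---|---|---|
| 0.05 | 0.0019 | 0.0029 | 0 |
| 0.10 | 0.0038 | 0.0058 | 0 |
| 0.20 | 0.0077 | 0.0115 | 0 |

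**3. If a difference persists at 6 weeks.** A residual of 0.02 at 6 weeks alone gives 0.02 × 91/365 = 0.005 QALY; 0.05 gives 0.0125. So the schedule is not blind to every benefit, but the estimate then rests on one score taken after the contrast has ended.

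**4. How long after.** Nominally 42 − 21 = 21 days. The windows allow as little as 35 − 24 = 11 days.

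**5. Effect of adding scores.**
- Day 21 only: (21/2 + 21/2)d/365 = 21d/365. This is exact for a difference spanning days 0-21, and 21/14 = 1.5 times too high for one confined to days 7-21.
- Days 7 and 21, both showing d: (3.5 + 14 + 10.5)d/365 = 28d/365, i.e. 0.0038, 0.0077 and 0.0153 for the three values of d. This is 28/21 = 1.33 times the days 0-21 value and 28/14 = 2 times the days 7-21 value.
- Days 7 and 21, with no difference yet at day 7: (7 + 10.5)d/365 = 17.5d/365, or 17.5/14 = 1.25 times the days 7-21 value.

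The added scores turn a certain zero into a non-zero estimate. For a difference that stops abruptly they overstate it, mainly through the straight line from day 21 to day 42, so the interpolation rule has to be stated.

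**The case against.** The strongest reply is that the economic argument in the article is mostly about productivity. The Background expects earlier return to work, higher satisfaction and lower health care costs, and the Discussion sentence on earlier independence leads on to cost-effectiveness. The perspective is societal, iPCQ and iMCQ are completed at 6 weeks, and return to work and pain are asked at follow-up visits. This stands. A reader might infer that the economic evaluation cannot detect the benefit it was set up to find. The article does not support that: nowhere does it say the evaluation was designed to detect a QALY gain in the first weeks, and nothing shows that costs in that period are lost, since the recall periods of the cost questionnaires are not given.

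Three further readings go too far:
- One might take the end of week 1 to week 3 as the only time the arms differ. They also differ in week 1, and the Background presents the brace as the more comfortable option.
- One might say that at the 6-week score every patient has been free of immobilisation for at least 3 weeks. The windows allow 11 days.
- One might say that an early gain can never enter the result. It can if part of it persists to 6 weeks, which is plausible given the article's stiffness rationale.

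It is also fair that the size rests wholly on assumed utilities, that the trial is not sized for an economic endpoint, and that Table 2 and Fig. 2 are not shown. The text on timing is explicit, so an earlier EQ-5D is unlikely, but the schedule should be checked. None of this supplies a utility score between day 0 and week 6.

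**Conclusion.** The point holds in limited form. No utility is measured during the 21 days in which treatment differs, and a difference that resolves before the 6-week score contributes zero QALYs. For assumed differences of 0.05-0.20 the missed gain is about 0.002-0.008 QALY per patient if confined to days 7-21, and 0.003-0.012 if it spans days 0-21. These amounts are small, but if the arms are equal at 6 weeks and 6 months they are the whole QALY effect.

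The conclusion rests on an area-under-the-curve calculation, on EQ-5D scoring current health, and on no earlier EQ-5D in the schedule figures. Days 0-21 also takes allocation to occur on the day of trauma; the article has eligible patients start in a cast and allows evaluation in the outpatient department, so the contrast may begin somewhat later in some patients. The gap touches the QALY side of a secondary analysis only. The PRWE comparison and its sample size are unaffected. It is a cheap improvement, not a flaw that threatens the trial.

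**What to change.** Add EQ-5D in both arms at the same two times: at the existing 1-week contact and at 3 weeks. In the cast arm, the 3-week form should be completed before the cast comes off, because an answer given after removal may show little or no difference. The brace arm can answer by phone or online. Use both scores in the QALY calculation, and state how utility is interpolated between them and the 6-week score, since a straight line from day 21 to day 42 can overstate a short-lived difference.

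Cost: one short questionnaire twice per patient and one extra remote contact for the brace arm at 3 weeks; no extra visit or procedure.

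If this is no longer feasible, state in the analysis plan and the report that the cost-utility result cannot reflect utility differences that resolve before the 6-week score, and do not read a zero QALY difference as evidence that no early difference existed.

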**Fig. 1 Fig1:**

Inclusion procedure at ED

**Fig. 2 Fig2:**
[figure not shown]
Follow-up scheme

### Sample and selection criteria

The study population is defined as adult patients, between 18 and 50 years old, with a non- or minimally displaced DRF. Patients above the age of 50 are excluded from this study to eliminate bias by osteoporosis.

Inclusion criteria are:18–50 years (to eliminate osteoporosis)Primary non- or minimally displaced DRFIndependent for activities of daily living

Exclusion criteria are:Fracture of the contralateral wristIpsilateral fractures, proximal of the DRFPre-existent abnormalities or functional deficits of the fractured wristOpen fracturesLanguage disability to understand the Dutch patient information and questionnaires

Patients with a non- or minimally displaced DRF will be initially managed on the emergency department (ED) by X-ray and cast immobilisation in a lower arm cast in a neutral position [32]. Non- or minimally displaced will be classified according to the guidelines of the American Association of Orthopedic Surgeons (AAOS) and the Dutch guidelines. They state that the following radiographic parameters do not need a reduction before immobilisation: radial shortening <3 mm, dorsal tilt <10°, volar tilt <20° or intra-articular step-off <2 mm, >15° radial inclination, intact radiocarpal alignment and absence of radial or dorsal/volar translation [4, 34].

Evaluation of eligible patients will take place either at the ED or at the outpatient department of Spaarne Gasthuis, Haarlem/Hoofddorp, Amsterdam UMC, location AMC, Amsterdam and Maasstad Hospital, Rotterdam, the Netherlands. Patients with a DRF will be treated by the physician on call at the ED. Patients are eligible if they meet the in- and exclusion criteria. If a patient is eligible, he/she will start with the standard treatment for non- or minimally displaced DRF, namely cast immobilisation.

Patients can only participate if the DRF is non- or minimally displaced. They will receive written information and an informed consent form from the attending physician/the clinical investigator/research assistant. When the X-ray taken at the ED showed non- or minimal displacement, informed consent will be signed and eligible patients will be randomised (Fig. 1). An independent research assistant will perform a concealed permuted block randomisation by using a secured computer-generated randomisation schedule after stratification for gender and age. Allocation will be at random in four blocks (Table 1). In total, 1 week of brace immobilisation, if assigned to the intervention group, or 3 weeks of cast immobilisation, if assigned to the control group, will be executed. It is expected that all patients can be included within 1–1.5 year from the start of the study.

**Table 1 Tab1:** Stratification by gender and age

Patient characteristics			Randomisation
List 1	Male	< 30 y.o.a	ABAB AABB ABBA BABA BAAB
List 2	Male	> 30 y.o.a	BAAB BBAA ABAB AABB ABBA
List 3	Female	< 30 y.o.a	AABB ABBA BAAB BBAA BABA
List 4	Female	> 30 y.o.a	ABBA BABA ABAB AABB AABB

*y.o.a.* years of age, *A* 1 week of brace immobilisation, *B* 3 weeks of cast immobilisation

The inclusion and follow-up schedule are visualised in Fig. 2 and Table 2. All patients will be followed for 6 months in total. Assessments will occur at the time of admission at the ED, assessment by phone consult in 1 week after trauma (5–9-day window) in case of inclusion in the intervention group (e.g. 1 week of brace immobilisation), physical assessment in case of the control group (e.g. 3 weeks of cast immobilisation) at 1 (5–9-day window) and 3 weeks (18–24-day window). All patients will be physically assessed at 6 weeks (5–7-week window) and 6 months (5–7-month window) after the start of treatment. After removal of the brace or cast, additional physiotherapy is advised and exercises to train wrist function will be given.

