## Methods/design

The aim of this trial is to evaluate the non-inferiority of 1 week of brace immobilisation in patients with non- or minimally displaced distal radius fractures. As the ideal treatment of DRF is short, safe and will lead to an early return to work or daily activities, non-inferiority of 1 week of brace immobilisation will be considered superior to a longer period of immobilisation. This hypothesis was also supported by the previous study performed by this study group [22].

Primary outcome is:

Patient-reported outcome measured by the PRWE score after 6 months

Secondary outcomes:

Patient-reported outcome measured by the Quick Disabilities of the Arm, Shoulder and Hand score (qDASH) after 6 weeks and 6 monthsPatient-reported outcome measured by the PRWE score after 6 weeksRange of motion after 6 weeks and 6 monthsPatient-reported pain score (VAS score) at arrival at ED, after cast/brace is applied, in the first week after brace/cast removal, at 6 weeks and 6 monthsRadiological outcome at 6 weeks and 6 monthsComplicationsCost-effectiveness measured by EQ-5D, iMCQ and iPCQ questionnaires

The PRWE is a validated 15-item (scored 1–10) self-reported questionnaire and is the best questionnaire for evaluating the patient-reported outcome in case of DRFs [23, 24]. Patients rate their outcome on a 0–10 scale on pain and functional outcome, and scores will be transformed to a 0–100 score. A higher score indicates greater disability. The DASH Outcome Measure is a validated 30-item self-reported questionnaire for patients with disorders of the arm, shoulder and hand [25, 26]. The QuickDASH (qDASH) is the shortened version of the DASH Outcome Measure, using 11 items instead of 30 (scored 1–5) to measure pain and functional outcome. At least 10 of the 11 items must be completed to calculate a score. The scores will be transformed to a 0–100. A higher score indicates greater disability.

Range of motion will be measured by using a goniometer: volar/dorsal flexion, radial/ulnar deviation and pronation/supination will be determined. Patient-reported pain score will be measured by using the VAS score. VAS score is a widely used method for pain assessments. Patients score their pain on a scale of 1–10. A higher score indicated a higher level of pain. The VAS score will be measured on the ED at arrival and after application of the brace of cast. Patients will also receive a dairy after cast removal to record their pain score.

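### Before 6 weeks the brace arm is checked less often for complications and return to work, and secondary displacement omits the volar tilt limit used for eligibility

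*Protocol article*

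**What the plan says.** **Contacts.** Under Sample and selection criteria the brace arm has "assessment by phone consult in 1 week after trauma (5–9-day window) in case of inclusion in the intervention group". The cast arm has "physical assessment in case of the control group (e.g. 3 weeks of cast immobilisation) at 1 (5–9-day window) and 3 weeks (18–24-day window"). After that the arms share a schedule: "All patients will be physically assessed at 6 weeks (5–7-week window) and 6 months (5–7-month window) after the start of treatment".

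**What is asked.** The text after Table 2 in the same section says that at each follow-up visit "the research coordinator or research assistant will ascertain patient status", which covers re-interventions, adverse events and complications, and deaths, with verification in the medical records. The same paragraph says that patients are asked about current pain, physiotherapy and return to work.

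**Pain.** Methods/design lists five VAS time points: arrival at the ED, after the device is applied, "in the first week after brace/cast removal", 6 weeks and 6 months. The sentence on the diary mentions cast removal only.

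**Displacement.** The outcome definition in Methods/design reads "Complications contain secondary displacement (radial shortening > 3 mm, dorsal tilt > 10° or intra-articular step-off > 2 mm"). The eligibility limits under Sample and selection criteria include "radial shortening <3 mm, dorsal tilt <10°, volar tilt <20° or intra-articular step-off <2 mm", followed by radial inclination, radiocarpal alignment and translation. The Background also gives volar tilt below 20° as part of what makes a fracture non- or minimally displaced.

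**X-rays.** Films are planned at the ED, 6 weeks and 6 months, with no difference by arm. Volar tilt is measured in degrees on them.

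**The concern.** The Background asks whether one week of brace is safe and leads to earlier return to work. It names secondary displacement and pain as the harms that clinicians fear. These claims rest on secondary outcomes, so both arms should be observed with equal intensity.

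They are not, before 6 weeks. A tendinitis or nerve complaint that starts and settles between weeks 1 and 6 has a scheduled chance of being recorded in the cast arm (week 3) and none in the brace arm. For such events the difference in looks favours the brace. For return to work it can do the opposite. A brace patient back at work in week 2 has no stated contact at which to report it until weeks 5 to 7, so the benefit that the trial hopes to show may be blurred.

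Two smaller matters affect how the same outcomes are read. A fracture that passes the volar tilt limit set for entry is not counted as secondarily displaced. The VAS tied to device removal is taken at different times after injury in the two arms.

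**Working it through.** **1. Stated figure.** The point disputes no number in the plan. To confirm that the primary outcome is untouched, take the inputs under Sample size calculation: margin 10.0, SD 14.0, power 90%, alpha 5%. The section does not state sidedness, so one-sided is assumed.

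n per arm = 2 × (1.645 + 1.282)² × 14² / 10² ≈ 33.6, rounded up to 34.

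This matches the stated 34. PRWE at 6 months is collected in the same window in both arms, so nothing below changes it.

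**2. Contacts after the ED, as stated.**

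| Time | Brace (1 week) | Cast (3 weeks) |
|---|---|---|
| Week 1 (days 5–9) | phone | in person |
| Week 3 (days 18–24) | none stated | in person |
| 6 weeks (weeks 5–7) | in person | in person |
| 6 months (months 5–7) | in person | in person |
| Total | 3 (2 in person) | 4 (4 in person) |
| Before 6 weeks | 1 (0 in person) | 2 (2 in person) |

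The nominal gap before the 6-week visit is 42 − 7 = 35 days in the brace arm and 42 − 21 = 21 days in the cast arm. Using the visit windows, the shortest possible gap is 35 − 9 = 26 days against 35 − 24 = 11 days.

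**3. What unequal looks could do to complication counts (illustration only).** The document gives no expected complication rate and no detection rate. Suppose that the true rate p is equal in both arms, and that the brace schedule detects a fraction s of what the cast schedule detects. The apparent difference, brace minus cast, is p × (s − 1).

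- p = 5%, s = 0.9: −0.5 percentage points.
- p = 10%, s = 0.5 to 0.9: −5 to −1 points. With 37 per arm that is 1.9 to 3.3 events against 3.7.
- p = 20%, s = 0.5: −10 points.

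These values show the direction and how wide the range is. They are not an estimate. They apply only to events whose detection depends on a visit.

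**4. Timing of the post-removal VAS.** With removal at day 7 or day 21, the first week afterwards is days 8–14 (brace) or days 22–28 (cast), 14 days apart. If removal is assumed to fall within the visit windows, the spans are days 5 to 9 + 7 = 16 and days 18 to 24 + 7 = 31, with no overlap. If pain fell by an assumed 0.25 to 1.0 VAS points per week, the 2-week offset alone would give 2 × 0.25 = 0.5 to 2 × 1.0 = 2.0 points against the brace.

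**5. Displacement definitions side by side.**

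| Parameter | Eligibility limit | Counts as secondary displacement |
|---|---|---|
| Radial shortening | <3 mm | >3 mm |
| Dorsal tilt | <10° | >10° |
| Intra-articular step-off | <2 mm | >2 mm |
| Volar tilt | <20° | not listed |
| Radial inclination | >15° | not listed |
| Radiocarpal alignment, translation | intact / absent | not listed |

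A fracture below 20° volar tilt at entry and above 20° at 6 weeks no longer meets the trial's own description of minimally displaced, yet it is not a complication. The rule is the same in both arms.

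**The case against.** The strongest reply is that most of the observation is matched. The ED, week 1, 6 weeks and 6 months are common to both arms, and week 1 differs in mode, not in time. The only contact that one arm lacks is the 3-week visit, which coincides with the end of cast treatment. Most listed complications persist or leave a record (non-union, re-intervention, CRPS, tendon rupture, nerve lesion) and can be found at the common visits. Records are checked, and the iPCQ at 6 weeks and 6 months covers work absence in both arms. Figure 2 and Table 2 are not available here and could show further contacts. All of this stands. It narrows the concern to minor or transient events and to the timing of early return to work, but does not remove it. The text itself assigns early contacts by arm. Record checks do not fully equalise the arms either, because the extra hospital visits themselves generate record entries.

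A reader might infer more than the document supports:

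- *That displacement is under-detected in the brace arm*, because the Background says that 90% of secondary displacement occurs in the first 2 weeks. The planned X-rays do not differ by arm, and none is listed at weeks 1 or 3. The Background adds that the figure concerns predominantly displaced and reduced fractures, and that displacement is very uncommon in this population.
- *That volar displacement goes unseen.* Volar tilt is measured and reported as a radiological outcome. Only its classification as a complication is missing.
- *That the pain comparison as a whole is confounded.* One of five VAS points is anchored to removal. Pain on leaving the device is a legitimate question, and the 6-week and 6-month scores are time-matched.

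**Conclusion.** The point holds in a limited form. On the stated schedule the cast arm has two physical assessments before 6 weeks and the brace arm one phone consult. Minor or transient complications and early return to work are therefore ascertained unequally by allocation. The direction is plausible: in favour of the brace for such complications, and possibly against it for return to work. The size cannot be derived, because no complication rate or detection rate is given.

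The secondary displacement definition is incomplete when set against the trial's own eligibility limits. This applies equally to both arms and does not bias the comparison between them. The post-removal VAS falls about 2 weeks earlier after injury in the brace arm and can be read only as a removal-anchored measure.

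The conclusion assumes that the schedule in the text is complete and that devices come off near weeks 1 and 3. The primary outcome, the sample size and displacement on the planned X-rays are not affected.

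**What to change.** 1. **Complications and return to work.** Base the between-arm comparison on contacts common to both arms, recording the onset date of each event and the date of return to work. Alternatively, use the same short status check, by phone or e-form, at weeks 1 and 3 in both arms. This concerns data collection only and leaves the clinical visits as they are. The first option needs no extra contact but gives up the week-3 information. The second costs one brief extra contact per brace patient, 37 in all.
2. **Secondary displacement.** Reconcile the outcome definition in Methods/design with the limits in the Background and in Sample and selection criteria. Either align them or say why volar tilt and the other unlisted parameters are left out. The tilt values are already measured, so for volar tilt this costs a change of text only.
3. **Pain.** Label the VAS in the week after removal as event-anchored, make clear that the diary applies to both arms, and rest the between-arm pain comparison on the 6-week and 6-month scores. No new data are needed beyond the diary already planned.
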